**Table 3: Definitions of causality**

| Relationship     | Description                                                                                                                                                                                                                                                                                                     | Event Type |
|------------------|-----------------------------------------------------------------------------------------------------------------------------------------------------------------------------------------------------------------------------------------------------------------------------------------------------------------|------------|
| Unrelated | There is no evidence of any causal relationship                                                                                                                                                                                                                                                                 | SAE        |
| Unlikely  | There is little evidence to suggest there is a causal relationship (e.g. the event did not occur within a reasonable time after administration of the trial medication). There is another reasonable explanation for the event (e.g. the patient's clinical condition, other concomitant treatment).            | SAE        |
| Possible  | There is some evidence to suggest a causal relationship (e.g. because the event occurs within a reasonable time after administration of the trial medication). However, the influence of other factors may have contributed to the event (e.g. the patient's clinical condition, other concomitant treatments). | SAR        |
| Probable  | There is evidence to suggest a causal relationship and the                                                                                                                                                                                                                                                      | SAR        |

|                   |                                                                                                                    |     |
|-------------------|--------------------------------------------------------------------------------------------------------------------|-----|
|                   | influence of other factors is unlikely.                                                                            |     |
| Definitely | There is clear evidence to suggest a causal relationship and other possible contributing factors can be ruled out. | SAR |

**(d) Notification**

The appropriate Trials Unit should be notified within one working day of the investigator becoming aware of an event that requires expedited reporting. Investigators should notify the appropriate Trials Unit of all SAEs occurring during the trial.

**Notification Procedure:**

1. The SAE form must be completed by the Investigator (consultant named on the signature list and delegation of responsibilities log who is responsible for the patient's care), with due care being paid to the grading, causality and expectedness of the event as outlined above. In the absence of the responsible investigator the form should be completed and signed by a member of the site trial team. The responsible investigator should subsequently check the SAE form, make changes as appropriate, sign and then re-fax to the appropriate Trials Unit as soon as possible. The initial report shall be followed by detailed, written reports as appropriate.
2. Send the SAE form by fax to the appropriate Trials Unit:
 

|                                                                            |                                                                                                                                |
|----------------------------------------------------------------------------|--------------------------------------------------------------------------------------------------------------------------------|
| MRC Clinical Trials Unit
INSERM SC10-US019
PHPT | Fax Number: [name]
Fax Number: [name]
Fax Number: [name] |
|----------------------------------------------------------------------------|--------------------------------------------------------------------------------------------------------------------------------|
3. Follow-up of events: Patients must be followed-up until clinical recovery is complete and laboratory results have returned to normal or baseline, or until the event has stabilised. Follow-up should continue after completion of protocol treatment if necessary. Follow-up information should be noted on a further SAE form by ticking the box marked 'follow-up' and faxing to the appropriate Trials Unit as information becomes available. Extra annotated information and/or copies of test results may be provided separately. The patient must be identified by trial number and date of birth only. The patient's name should not be used on any correspondence.
4. Staff at the institution must notify their local research ethics committee of the event (as per the institution's standard local procedure).

**10.4 Trials Units' responsibilities**

Medically qualified staff at the Trials Units and the Chief Investigator (or a medically qualified delegate) will review all SAE reports received. The causality assessment given by the local Investigator at the hospital cannot be overruled and in the case of disagreement, both opinions will be provided in any subsequent reports.

The MRC Clinical Trials Unit at UCL, INSERM SC10 and PHPT are undertaking the duties of trial sponsor and are responsible for pharmacovigilance in the countries they co-ordinate and are responsible for the reporting of SUSARs and other SARs to the regulatory authorities of countries in which the trial is taking place and the national research ethics committees as appropriate. In certain instances this responsibility will be delegated to a national co-ordinator.

The Trials Units will also keep all investigators informed of any safety issues that arise during the course of the trial.

Trials Units will comply with any further reporting requirements of the countries they co-ordinate.

**Figure 1: Safety Reporting Flowchart**

[figure not shown]

# 11 STATISTICAL CONSIDERATIONS

## 11.1 Method of Randomisation

Randomisation (1:1) will be performed centrally by the MRC Clinical Trials Unit, according to a computer-generated randomisation list, using random permuted blocks, stratified by age at randomisation (8-12, 13-17, 18-24 years) and by African vs. non-African country.

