## **5.3 Siblings**

If more than one child from the same family is eligible and carers give consent to enrolment into the trial, they will be enrolled to the same arm of the study in order to avoid problems caused by one sibling taking weekend breaks and not the other. Please indicate this in the relevant section of the randomisation form. (See section 11.1).

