## 11.3 Sample size

This phase II/III trial will enrol a minimum of 160 young people, at least 80 per arm.

Assuming 90% of young people in the continuous ART arm and in the SCT arm maintain HIV-1 RNA  $< 50$  c/ml to week 48, 155 young people will provide at least 80% power to exclude a difference of 12% between the two arms (i.e. to exclude suppression rates of less than 78% in the SCT arm) (one-sided  $\alpha = 0.05$ ) [37]. A minimum of **160 (80 per arm) young people will be enrolled** to allow for loss to follow-up (in previous PENTA trials loss to follow-up has been less than 3%).

The power calculations are based on the assumption that 90% of patients in the continuous ART arm will remain virally suppressed to week 48. Any decrease in this percentage is likely to under

power the study and could lead to an equivocal result, as could other changes to the assumptions. The table below gives an indication of the power to exclude a difference of 12% between the two arms for different sample sizes and levels of suppression in the continuous ART arm:

| Total sample size | Power by level of suppression in control arm |                |                |                |                |                |
|-------------------|----------------------------------------------|----------------|----------------|----------------|----------------|----------------|
|                   | 90% suppressed                               | 89% suppressed | 88% suppressed | 87% suppressed | 86% suppressed | 85% suppressed |
| 160               | 80                                           | 77             | 74             | 72             | 69             | 67             |
| 170               | 82                                           | 79             | 76             | 74             | 72             | 69             |
| 180               | 84                                           | 81             | 79             | 76             | 74             | 72             |
| 190               | 86                                           | 83             | 81             | 78             | 75             | 74             |
| 200               | 87                                           | 85             | 82             | 80             | 78             | 76             |
| 210               | 89                                           | 86             | 84             | 82             | 79             | 77             |

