| 220               | 90                                           | 88             | 85             | 83             | 81             | 79             |

A sample size of 220 participants would increase the power of the study by at least 10% for varying levels of suppression. The TSC and IDMC therefore agreed that the study should remain open to randomisation until the end of the defined recruitment period even should the total number of participants enrolled exceed 160, as this would enhance the power of the study as indicated in the table above. The total recruitment target should be at least 160 but not exceed 220 participants.

The trial is not formally powered to detect differences between continuous ART and SCT, but to exclude substantial virological disadvantages (i.e. HIV-1 RNA suppression rates (<50 c/ml) of less than 78%) to the SCT arm by following a 5 days on, 2 day off strategy i.e. a non-inferiority trial.

A non-inferiority margin of 12% was chosen to represent a clinically acceptable difference in the rate of virological suppression <50 c/ml between the two arms, and to allow the trial to be adequately powered and feasible to conduct based on estimates of available young people followed in PENTA centres.

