## **11.6 Analysis plan**

Intention-to-treat analyses will be performed on all randomised participants. Statistical methods include:

- Descriptive statistics for the summary of baseline characteristics
- Fishers exact test and logistic regression models for the analysis of binary outcome variables
- Analysis of variance and linear regression models for the analysis of continuous outcome variables, adjusting for baseline
- Poisson regression for the analysis of the incidence rate of clinical/adverse events
- Log rank test and proportional hazards regression models for the analysis of time to event variables

The incidence rate of clinical/adverse events will be summarised by body system and randomised arm. First events (in terms of time to first event) and all events will be considered.

Major resistance mutations will be defined by the current IAS-USA list.

The primary outcome for the main study is HIV-1 RNA  $\geq 50$  c/ml (confirmed on a separate sample within 1 week) at any of week 4, 12, 24, 36 or 48. This outcome only considers HIV-1 RNA measurements at these time points due to the difference in viral load monitoring in the pilot phase and the main trial. However if a young person enrolled in the pilot phase has an HIV-1 RNA  $\geq 50$  copies/ml at weeks 1, 2 or 3 (reproducible on the same sample) or at week 8 (confirmed on a separate sample within 1 week) they will be considered as reaching the primary outcome at week 4 and 12 respectively. All participants will be analysed in the arm to which they were randomised (intention to treat).

A full Statistical Analysis Plan (SAP) will be developed as a separate document.

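### The listed analyses name neither the randomisation strata nor an allowance for siblings placed in the same arm; both effects on the interval are probably small, but the sibling one favours declaring non-inferiority

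*Combined protocol and SAP*

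**What the plan says.** Section 11.1 (Method of Randomisation) describes central 1:1 allocation in random permuted blocks, "stratified by age at randomisation (8-12, 13-17, 18-24 years) and by African vs. non-African country". It says nothing about families.

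Section 5.3 (Siblings) says of eligible siblings that "they will be enrolled to the same arm of the study in order to avoid problems caused by one sibling" taking weekend breaks and another not. It asks sites to note this on the randomisation form and refers the reader to 11.1.

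Section 11.6 (Analysis plan) gives "Fishers exact test and logistic regression models for the analysis of binary outcome variables", log-rank and proportional hazards for time to event, Poisson regression for event rates, and linear models for continuous outcomes. The only adjustment named is for the baseline value of continuous outcomes. The section presents its methods as an open list and leaves the detail to a separate SAP, which is not in the supplied text.

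Section 11.3 (Sample size) sets the power: "Assuming 90% of young people in the continuous ART arm and in the SCT arm maintain HIV-1 RNA" below 50 c/ml to week 48, and on that basis "155 young people will provide at least 80% power to exclude a difference of 12% between the two arms". Alpha is one-sided 0.05. At least 160 are to be enrolled, and "The total recruitment target should be at least 160 but not exceed 220 participants".

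**The concern.** An analysis should reflect how participants were allocated. There are two departures here, and they act in opposite directions.

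- **Strata.** Stratified permuted blocks balance the arms on age band and region. If risk differs between strata, an unstratified standard error includes between-stratum variation that the design has removed. The interval is then wider than it need be, and some power is lost.
- **Siblings.** Two siblings in one arm share a household and often a carer. Section 2.6 treats non-adherence as a route to rebound, and the carer questionnaires in Appendix 4 recognise that carers may give the medicines. Positively correlated outcomes are therefore plausible. A standard error that assumes independence is then too small, the interval too narrow, and the 12-point margin excluded more often than the nominal error allows.

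In a non-inferiority trial the second effect matters more, because it leans towards the conclusion that the trial hopes to reach. The broken cross-reference adds to the problem: a reader cannot tell from 11.1 how a family is allocated, or how siblings in different age bands use the block lists.

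**Working it through.** **1. The plan's own figure.** Inputs from section 11.3: suppression 0.90 in both arms, margin 0.12, one-sided alpha 0.05, power 80%. With unpooled variance and independent participants:

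n per arm = 2 × 0.9 × 0.1 × (1.645 + 0.842)² / 0.12² = 77.28, so 154.6 in total against 155 stated.

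Power at 155: SE = √(0.18/77.5) = 0.0482; 0.12/0.0482 − 1.645 = 0.845; Φ = 80.1%.

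The figure reproduces under independence, so it contains no allowance for families. The same formula gives 81.2% at 160, where the plan's table has 80; the gap does not affect this point.

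**2. Leaving out the strata.** The documents give no stratum risks, so these are assumed. The measure is the ratio of mean within-stratum variance to total variance.

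Example: six equal strata with suppression 95, 90, 85, 95, 90 and 85%. Mean within-stratum variance = (0.0475 + 0.0900 + 0.1275)/3 = 0.0883. Total = 0.9 × 0.1 = 0.09. Ratio = 0.98.

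Assumed patterns with stratum failure risks spread from 5–15% (narrowest) to 2–30% (widest) give ratios of 0.991, 0.968 and 0.939. Power at 155 = Φ(0.12/√(0.18 × ratio/77.5) − 1.645):

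| Variance ratio | Power at 155, stratified | Gain over 80.1% |
|---|---|---|
| 0.991 | 80.4% | 0.3 points |
| 0.968 | 81.2% | 1.1 points |
| 0.939 | 82.2% | 2.1 points |

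The actual one-sided error of the unstratified analysis, 1 − Φ(1.645/√ratio), is 0.049, 0.047 and 0.045, which is conservative.

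**3. Ignoring same-arm siblings.** The documents give neither the share f of participants in sibling pairs nor the within-family correlation (ICC). Assume f of 5–20% and ICC of 0.1–0.5. Design effect DE = 1 + f × ICC. Error of an analysis that assumes independence = 1 − Φ(1.645/√DE). Power of an analysis with the correct standard error = Φ(0.12/√(0.18 × DE/77.5) − 1.645).

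| f | ICC | DE | One-sided error | Power at 155 |
|---|---|---|---|---|
| 5% | 0.1 | 1.005 | 0.050 | 79.9% |
| 10% | 0.5 | 1.05 | 0.054 | 78.4% |
| 20% | 0.5 | 1.10 | 0.058 | 76.7% |

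Last row: SE = √(0.18 × 1.10/77.5) = 0.0506; 0.12/0.0506 = 2.374; 2.374 − 1.645 = 0.729; Φ = 76.7%. With that DE, 80% power needs 154.6 × 1.10 = 170.02, so 171 participants. At 160 enrolled, the half-width of the 90% interval goes from 1.645 × √(0.18/80) = 7.80 points to 7.80 × √1.10 = 8.18. With no siblings there is no effect.

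**4. Both together.** The product of the two factors runs from 0.939 × 1.005 = 0.944 to 0.991 × 1.10 = 1.090. Square roots are 0.97 and 1.04, so a standard error that ignores both is between about 3% too large and 4% too small. No net change lies within the range.

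**5. How much stratification the data can bear.** At 10% failure, 160 participants yield about 16 events. Over six strata and two arms that is 16/12 = 1.3 per cell, so fully stratum-specific estimates would be unstable.

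**The case against.** The strongest reply is that section 11.6 makes no choice at all. Its list is open, the regression models on it can carry strata and clustered errors, and a separate SAP was to follow. A reader might infer that the plan opted for an unstratified analysis, or decided to treat siblings as independently randomised. The text does not support that. It is silent, and the separate SAP may have dealt with both matters. For the same reason nobody can say that the interval is wrong, only that it would be slightly mis-sized if the listed methods were run without these terms. Section 11.6 does not even say which method yields the interval for the 12-point difference.

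A reader might also infer that a later sibling's arm is known before consent, so that families can select by arm. The trial is open and sequential entry is not excluded, but 5.3 is equally consistent with a single allocation for the whole family. Selection is possible and not established.

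It is fair too that every effect size above rests on assumed inputs, that the two effects oppose each other, and that recruitment above 160 would absorb the loss: with DE = 1.10, power at 220 is about 88%.

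What survives is that neither the strata nor the families appear in the analysis or the sample size, and that the cross-reference leads nowhere. Extra recruitment restores power but does not correct the inflated error of an analysis that ignores families. Nor can the two effects be relied on to cancel.

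**Conclusion.** The point holds as an omission with small, opposing numerical consequences. On the assumed stratum risks, adjusting for the randomisation factors is worth about 0.3 to 2.1 points of power at 155. On the assumed sibling share (5–20% of participants in pairs) and correlation (0.1–0.5), ignoring families gives a one-sided error of 0.050 to 0.058 against a nominal 0.05, and power at 155 with a correct standard error falls from 80% to as low as 77%. Only the sibling effect works against the protection that a non-inferiority test should give. Its true size depends on how many sibling sets enrolled, which the documents do not report. Because the remedy uses data already collected and costs almost nothing, it should be made, but the omission does not by itself put the trial's conclusion in doubt.

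**What to change.** 1. Estimate the primary risk difference adjusted for the randomisation factors, either with Mantel-Haenszel weights or from a model with age band and African/non-African region as main effects. With about 16 expected events, main effects are safer than six separate stratum estimates.
2. Use family-clustered robust standard errors for that estimate.
3. Add a sensitivity analysis that keeps only the first randomised sibling in each family.
4. State in 11.1 how siblings are allocated, so that the reference from 5.3 leads to a rule.
5. Settle items 1 to 3 in writing before the arms are compared, so that the choice cannot follow the result.

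The strata are known from randomisation, and 5.3 already has siblings marked on the randomisation form, so no new data are needed. The cost is SAP wording, one sentence in 11.1, a little more analysis work, and an interval that may widen slightly from the clustering.

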## 11.2 Outcome measures

### Pilot Phase Outcome Measure:

- HIV-1 RNA  $\geq 50$  copies/ml, reproduced on a repeat test of the same sample off ART on the Monday following SCT at any of week 1, 2, 3 (see section 11.5 for more details).

### **Primary Outcome:**

- HIV-1 RNA  $\geq 50$  c/ml (confirmed on a separate sample within 1 week) at any of week 4, 12, 24, 36 or 48 (see section 11.6 for more details)

### **Secondary Outcomes:**

- HIV-1 RNA  $< 50$  c/ml at 24 and 48 week.
- Number of HIV mutations present at week 4, 12, 24, 36 or 48 conferring resistance to drugs taken at randomisation or during the trial
- Change in CD4 (absolute and percentage) from randomisation to 24 and 48 weeks
- Change in ART (defined as any change from the ART regimen at randomisation)
- Grade 3 or 4 clinical and laboratory adverse events.
- ART treatment modifying adverse events (all grades).
- New CDC stage B or C diagnosis or death
- Changes in fasting glucose, cholesterol, triglycerides, LDL, HDL and VLDL levels through 48 weeks
- Adherence, acceptability, and quality of life over 48 weeks as assessed by patient completed questionnaires
- HIV-1 RNA  $\geq 50$  c/ml (confirmed on a separate sample within 1 week) at any time throughout follow up.
- HIV-1 RNA  $< 50$  c/ml at 96 and 144 weeks.
- Adherence over the duration of the trial, as assessed by patient completed questionnaires.
- Change in CD4 (absolute and percentage) from randomisation to 96 and 144 weeks.

## 11.3 Sample size

This phase II/III trial will enrol a minimum of 160 young people, at least 80 per arm.

Assuming 90% of young people in the continuous ART arm and in the SCT arm maintain HIV-1 RNA  $< 50$  c/ml to week 48, 155 young people will provide at least 80% power to exclude a difference of 12% between the two arms (i.e. to exclude suppression rates of less than 78% in the SCT arm) (one-sided  $\alpha = 0.05$ ) [37]. A minimum of **160 (80 per arm) young people will be enrolled** to allow for loss to follow-up (in previous PENTA trials loss to follow-up has been less than 3%).

The power calculations are based on the assumption that 90% of patients in the continuous ART arm will remain virally suppressed to week 48. Any decrease in this percentage is likely to under

power the study and could lead to an equivocal result, as could other changes to the assumptions. The table below gives an indication of the power to exclude a difference of 12% between the two arms for different sample sizes and levels of suppression in the continuous ART arm:

| Total sample size | Power by level of suppression in control arm |                |                |                |                |                |
|-------------------|----------------------------------------------|----------------|----------------|----------------|----------------|----------------|
|                   | 90% suppressed                               | 89% suppressed | 88% suppressed | 87% suppressed | 86% suppressed | 85% suppressed |
| 160               | 80                                           | 77             | 74             | 72             | 69             | 67             |
| 170               | 82                                           | 79             | 76             | 74             | 72             | 69             |
| 180               | 84                                           | 81             | 79             | 76             | 74             | 72             |
| 190               | 86                                           | 83             | 81             | 78             | 75             | 74             |
| 200               | 87                                           | 85             | 82             | 80             | 78             | 76             |
| 210               | 89                                           | 86             | 84             | 82             | 79             | 77             |
| 220               | 90                                           | 88             | 85             | 83             | 81             | 79             |

A sample size of 220 participants would increase the power of the study by at least 10% for varying levels of suppression. The TSC and IDMC therefore agreed that the study should remain open to randomisation until the end of the defined recruitment period even should the total number of participants enrolled exceed 160, as this would enhance the power of the study as indicated in the table above. The total recruitment target should be at least 160 but not exceed 220 participants.

The trial is not formally powered to detect differences between continuous ART and SCT, but to exclude substantial virological disadvantages (i.e. HIV-1 RNA suppression rates (<50 c/ml) of less than 78%) to the SCT arm by following a 5 days on, 2 day off strategy i.e. a non-inferiority trial.

A non-inferiority margin of 12% was chosen to represent a clinically acceptable difference in the rate of virological suppression <50 c/ml between the two arms, and to allow the trial to be adequately powered and feasible to conduct based on estimates of available young people followed in PENTA centres.

